### Trial Design

Given the problems of underdiagnosis and undertreatment of dementia, which are expected to worsen with the growing number of aging adults globally [69], we chose a hybrid type 1 effectiveness-implementation design for this trial. In this design, the primary emphasis is on testing the intervention, with a secondary emphasis on exploring implementation-related factors [55]. We chose this design because it would be premature to conduct an implementation-only trial, given that the 5-Cog has previously been studied in 1200 individuals in only 1 urban primary care setting. The hybrid type 1 effectiveness-implementation design allows us to confirm the effectiveness of our intervention, while also hastening its potential to make needed impact in the “real world” through incorporating implementation examination prospectively [55]. The clinical effectiveness (in this case, meaning the degree of beneficial effect [70]) component of the trial will be completed using a pragmatic, cluster randomized design (randomized at the level of the clinic) with intervention clinics receiving the 5-Cog paradigm and control clinics receiving enhanced usual care (cognitive concern information and cognitive impairment detection education provided but no detection approach or clinical decision support tool implemented).

### Objectives

This trial’s three aims are to (1) test whether the 5-Cog paradigm used in primary care patients with cognitive concerns in diverse urban and rural environments and including individuals from racial and ethnic minority groups and those with socioeconomically disadvantaged backgrounds leads to an increased rate of MCI and dementia diagnoses; (2) explore the implementation context, process, and outcomes of the 5-Cog paradigm in diverse primary care clinics using mixed methods guided by the CFIR; and (3) assess the cost-effectiveness of the 5-Cog paradigm.

We hypothesize that this trial will demonstrate the 5-Cog paradigm’s effectiveness in increasing the diagnosis of MCI in dementia and primary care, its cost-effectiveness in achieving this outcome, and the range of factors shaping its successful implementation across diverse primary care settings.

## Methods

### Participants, Interventions, and Outcomes

#### Study Setting

The study is being carried out at primary care clinics affiliated with 2 large academic health systems: Montefiore Medical Center and Albert Einstein College of Medicine (hereafter referred to as Montefiore-Einstein) in the Bronx, New York, and Indiana University Health (IUH) in Indiana.

The Montefiore-Einstein clinics serve an urban population primarily composed of individuals from historically minoritized racial and ethnic groups (Hispanic/Latino and Black populations). Of note, these clinics serve Bronx County, which ranks last (62 out of 62) among New York State counties on health-related indicators [71] and has a significant poverty rate, affecting 1 in 4 older adults [72]. The IUH clinics are situated across both urban and rural settings. Within this network, 12 (75%) of the 16 selected clinics are located in regions scoring >60 on the national area deprivation index (score range 0-100; higher scores indicate higher deprivation) [73,74]. Notably, 2 (17%) of these 12 clinics are in areas with an area deprivation index score of >91, underscoring the profound level of need of these communities. Indiana health-related indicators show higher premature death, lower life expectancy, lower PCP and mental health provider availability, and lower median household income than the US average [74].

The study procedures are completed by research assistants (RAs), who are trained as CHWs and embedded in the clinics. This approach was chosen for its pragmatic value, reflecting reality in primary care settings in which CHWs are incorporated into clinical teams and may complete other screening questionnaires with patients [75,76] and because the 5-Cog components have been shown to be practical and feasible for administration by individuals who are not medical professionals and with minimal training [37,44,77]. The RAs at Montefiore-Einstein are bilingual in English and Spanish because of the high proportion of Spanish-speaking participants at this site. All study materials were translated from English into Spanish and back translated to ensure language fidelity.

#### Eligibility and Screening

Clinics are eligible to participate if they provide primary care (internal medicine or family medicine), not specialty care. Clinics primarily serving as residency teaching sites are excluded.

In keeping with the pragmatic nature of the trial, our individual-level eligibility criteria are designed to ensure that enrolled patients are those who would receive this intervention if it were part of usual care [78-80]. The 5-Cog intervention was designed to improve dementia diagnosis in ambulatory primary care settings. Individuals are excluded if they have a prior diagnosis of dementia or reside in a nursing home. Nursing home residents are excluded because they already have a high prevalence of diagnosed dementia (60%-90%) [81] and largely do not receive primary care from ambulatory clinics because of their mobility and cognitive limitations [82]. To be eligible for our 5-Cog effectiveness study, individuals must be aged ≥65 years, have no prior diagnosis of dementia, speak English (Montefiore-Einstein or IUH) or Spanish (Montefiore-Einstein only), have a scheduled primary care office visit, and endorse a cognitive concern via a subjective cognitive concern questionnaire (SCQ) [32,83]. Initial screening is completed by RAs via prospective EMR review of patients scheduled at each clinic and confirmed through screening telephone calls.

Implementation study participants will be recruited from among patients, caregivers, clinicians, clinic staff, clinical leaders, clinical informatics staff, and administrative leaders. The exclusion criteria are the same as those for the effectiveness study.

Textbox 1 lists the complete individual-level inclusion and exclusion criteria, including the SCQ.

Inclusion and exclusion criteria.
**Effectiveness study**
Individual-level inclusion criteriaAged ≥65 yearsEnglish or Spanish speaking (Albert Einstein College of Medicine and Montefiore Medical Center will enroll English- and Spanish-speaking patients; Indiana University Health will enroll only English-speaking patients)Have a cognitive concern: subjective cognitive concern questionnaire result is positive (≥1 of the following: “Are you concerned about your memory?”—the chosen response is yes; “Are your loved ones concerned about your memory?”—the chosen response is yes; and “Is your mind as clear as it used to be?”—the chosen response is no)Individual-level exclusion criteriaPrior diagnosis of dementia (as recorded in the electronic medical record or reported by primary care provider; the prior diagnosis of mild cognitive impairment is not an exclusion criterion, but the effectiveness outcome is only counted if a participant previously diagnosed with mild cognitive impairment is assigned a new diagnosis of dementia)Nursing facility resident
**Implementation study**
Individual-level inclusion criteriaPatients who have undergone the 5-Cog battery, caregivers of these patients, clinicians, clinic staff, clinical leaders, clinical informatics staff, and administrative leaders at each of the randomized primary care practicesAbility to provide informed consentIndividual-level exclusion criteriaPrior diagnosis of dementia (as recorded in the electronic medical record or reported by primary care provider; the prior diagnosis of mild cognitive impairment is not an exclusion)Nursing facility resident

#### Recruitment of Clinics and Patients

The study team actively recruited clinics in the Bronx and Indiana to participate through contacting their administrative leadership to discuss the study. Generally, 1 to 3 meetings were held with clinic leadership and practicing clinicians to introduce the study and secure the clinic’s commitment to participate.

All individual patient recruitment for the effectiveness study is passive. RAs review a clinic’s scheduled patients via the EMR to determine which patients seem to meet the eligibility criteria and contact potentially eligible patients by telephone within 1 week before their scheduled office visit. The patient is informed that the caller is working with the patient’s primary care practice to assess cognitive concerns. The patient is asked to confirm that they plan to keep their upcoming clinic appointment. If they have decided to change the appointment, cognitive concerns are not assessed. If the patient confirms their scheduled appointment, the RA administers the SCQ (Textbox 1). The patient is free to decline to answer, at which point the call is ended. When the patient answers the questions, the results are documented in the EMR. In the clinics randomized to the control arm, patients who have answered the SCQ are considered recruited; and if their SCQ result is positive, they are considered enrolled once they show up to their scheduled clinic appointment. In the clinics randomized to the intervention arm, patients with a positive cognitive concern are invited to undergo additional cognitive screening (the 5-Cog battery) at the clinic on the day of their office visit, just before they see their care provider. Patients who agree are considered recruited, with enrollment confirmed once they complete their scheduled office visit. In both arms, patients who do not show up to their scheduled clinic appointment after a positive SCQ result are not considered enrolled. If these patients have another scheduled clinic appointment during the study period at their clinic, they are eligible to be rerecruited and enrolled at this time (RAs will call and confirm SCQ responses before this visit).

Implementation study participants will be actively recruited from intervention sites through snowball sampling among different types of key informants mentioned previously. In addition, we will collect quantitative implementation surveys from as many clinicians and staff as possible at the intervention clinics.

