#### Participant Timeline

The 22 participating clinics were randomized in year 1 of the study. These clinics are onboarded in waves throughout the 5-year study period. The time period over which each clinic will experience active study recruitment (with the goal of enrolling 300 patients per clinic) is anticipated to vary from 3 to 12 months, depending on clinic size.

For individual patients in the effectiveness study, the initial screening and recruitment telephone call takes place within 1 week before a patient’s scheduled primary care visit and takes 10 to 15 minutes. Patients are then considered enrolled when they complete their scheduled PCP clinic appointment.

At the intervention clinics, participating patients are asked to arrive up to 1 hour early for their scheduled visit to allow sufficient time for undergoing the 5-Cog battery before meeting their care provider. The 5-minute assessment is completed at the clinic before the appointment.

In both intervention and control groups, patients remain enrolled for 90 days. Study outcomes are ascertained at 90 days (primary and secondary end points), at which point the enrolled patients are considered to have completed participation. This time window was selected because >95% of physician actions for dementia care were completed within this period in our initial trial [33].

Implementation study participants are enrolled when they consent to participate in a survey or an interview, and their enrollment is completed at its conclusion. Figure 2 depicts the study flow.

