##### EMR Data

We will collect EMR data on trial-enrolled patients aged ≥65 years receiving care in the participating practices after obtaining consent from the practice leadership and receiving a waiver from the institutional review board (IRB). Outcomes will be extracted and aggregated from the EMR. Deidentified analytic databases will be created and analyzed by investigators.

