#### Effectiveness Study: Statistical Plan

The baseline characteristics of the clinical sites as well as individual enrolled patients will be examined after the baseline measurement time point at the halfway point of target enrollment. It is possible that baseline differences between the groups or missing data will limit the value of data analysis of measurements. Effects on the power to detect differences in the primary outcome will be evaluated and communicated to the principal investigators (PIs), data safety monitoring board (DSMB), and NIH. Given the monitoring plans outlined in the Monitoring subsection, it is exceedingly unlikely that there will be baseline differences between the groups of a magnitude that could threaten the validity of the study.

We will evaluate the clinical effectiveness of the 5-Cog paradigm on new cognitive impairment detection by comparing the proportion of “new MCI and dementia diagnoses” by PCPs within 90 days after the clinic encounter in the 5-Cog paradigm group versus the enhanced usual care group using generalized linear mixed effects (GLME) models with a logit link to account for clinic-clustered data [99]. Using these models, odds ratios of new MCI and dementia diagnoses between the 5-Cog paradigm and enhanced usual care arms will be calculated and tested. We chose a 90-day cutoff because the majority of PCP actions occurred within the first 30 days in our recent RCT [33]. The 22 clinics are cluster randomized to either the 5-Cog paradigm or enhanced usual care arm, which can result in correlated data due to clustering of patients within clinics. This issue will be handled using random effects in the mixed models. Proportions of new MCI and dementia diagnoses for each treatment group will also be reported. We will perform an intention-to-treat analysis. As a secondary approach, we will also perform a per-protocol analysis. All estimates will be reported together with their 95% CIs. The same method will be used for the secondary outcome (“improved dementia care”).

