### Ethical Considerations

The Albert Einstein College of Medicine IRB approved this study (2022-14144) and serves as the IRB of record for both sites under a reliance agreement with the Indiana University IRB. This study will be conducted in accordance with federal publication and data-sharing policies and regulations. Regarding consent for participants, we received a waiver of informed consent from individual patients from the IRB to maintain the pragmatic design of the clinical trial. For the implementation part of the study, consent is obtained from all participants before completion of any study measures. Participants who consent for the implementation study receive US $25 in compensation for completed interviews. Outcomes will be extracted and aggregated from the EMR and will be deidentified. After the study is completed, the deidentified, archived data will be transmitted to and stored in a data repository with protections in place for patient confidentiality.

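### Agreeing to the 5-Cog is a condition of enrolment in intervention clinics only, so the comparison labelled intention-to-treat is open to selection after randomization

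*Protocol article*

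**What the plan says.** The protocol article, *Recruitment of Clinics and Patients*, sets the rules by arm.

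- **Control clinics.** Answering the telephone questionnaire is enough to count as recruited. The enrolment rule then reads: "if their SCQ result is positive, they are considered enrolled once they show up to their scheduled clinic appointment". No agreement to testing is needed.
- **Intervention clinics.** Patients with a positive SCQ are invited to the 5-Cog battery on the day of the visit. The enrolment rule reads: "Patients who agree are considered recruited, with enrollment confirmed once they complete their scheduled office visit".

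The individual eligibility criteria (Textbox 1) are the same for both arms and do not mention agreement to testing. *Participant Timeline* gives one visit trigger without distinction of arm, completion of the scheduled PCP appointment. It also says that the 22 clinics were randomized in year 1 and are onboarded in waves, so patients are recruited after allocation.

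On data, *EMR Data* says: "We will collect EMR data on trial-enrolled patients aged ≥65 years receiving care in the participating practices". On analysis, *Effectiveness Study: Statistical Plan* says: "We will perform an intention-to-treat analysis", with a per-protocol analysis as a secondary approach. *Masking* says that patients and PCPs at 5-Cog sites cannot be blinded.

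**The concern.** An SCQ-positive attender who does not want cognitive testing is in the control denominator but not in the intervention denominator. The step that removes this patient comes after clinic randomization and exists in one arm only. Randomizing clinics balances the populations from which patients come, but it does not balance willing patients in one arm against all patients in the other.

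Willingness may well be related to the outcome. Acceptors may be more worried or better supported, and so more likely to be diagnosed anyway. Decliners may be the more impaired, which would push the other way. A random clinic effect in the mixed model does not remove either bias. An intention-to-treat analysis keeps enrolled patients in their assigned arm, but it cannot restore patients who were never enrolled.

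At stake are the validity and size of the primary odds ratio, the secondary outcome (analysed by the same method), and the cost per case, which under *CEA and Economic Impact* uses the effect estimate from this model.

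**Working it through.** **Inputs from *Effectiveness Study: Statistical Plan* and *Planned Sample Size*:** primary outcome 14% v 2%, ICC 0.05, two-sided alpha 0.05, 22 clinics of 300 patients. With 1:1 allocation that is 11 clinics and 3300 patients per arm.

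**Assumed, because the article does not give it:** the share *a* of SCQ-positive attenders in intervention clinics who agree to the 5-Cog.

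**1. The plan's own figure.** Design effect = 1 + 299 × 0.05 = 15.95. Effective n = 3300 / 15.95 = 206.9 per arm. A pooled-variance z test of 14% v 2% then has 99.5% power, which reproduces the stated >99%. The planned odds ratio is (0.14/0.86) / (0.02/0.98) = 7.98.

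**2. Selection with no treatment effect.** Let all SCQ-positive attenders have a 2% rate, and let agreers be diagnosed at *r* times the decliners' rate. The decliner rate is 0.02 / (a·r + 1 − a), and the agreer rate is *r* times that. The odds ratio compares agreers with controls at 2%.

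| a | r | agreer rate | spurious OR |
|---|---|---|---|
| 70% | 2 | 2.35% | 1.18 |
| 70% | 0.5 | 1.54% | 0.77 |
| 50% | 2 | 2.67% | 1.34 |
| 50% | 0.5 | 1.33% | 0.66 |
| 50% | 3 | 3.00% | 1.52 |

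**3. Upper bound on spurious benefit.** The largest upward bias arises if decliners are never diagnosed, so that agreers have a rate of 0.02/a. At 70% uptake: 0.02/0.7 = 2.86%, OR = (0.0286/0.9714) / (0.02/0.98) = 1.44. At 50%: 0.02/0.5 = 4%, OR = (0.04/0.96) / (0.02/0.98) = 2.04.

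**4. Power if all SCQ-positive attenders are analysed.** Assume decliners in intervention clinics have the 2% control rate, and 300 attenders per clinic including decliners. Intervention rate = 0.14a + 0.02(1 − a).

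For the racial and ethnic minority subgroup, simple design-effect calculations do not reproduce the stated 81% (they give 72.6% to 99.0%, depending on how cluster size is handled). I therefore took 81% as given. An effective n of about 81 per arm gives 81% for 14% v 2% in the same z test, and I kept that n for the diluted rates.

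| a | intervention rate | difference (points) | OR | overall power | minority-subgroup power |
|---|---|---|---|---|---|
| 100% | 14.0% | 12.0 | 7.98 | 99.5% | 81% (stated) |
| 90% | 12.8% | 10.8 | 7.19 | 98.9% | 75% |
| 70% | 10.4% | 8.4 | 5.69 | 94.6% | 60% |
| 50% | 8.0% | 6.0 | 4.26 | 80.2% | 42% |

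**The case against.** Several points on the other side are sound.

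- **Visit trigger.** A reader might infer that the arms also differ in attending versus completing the visit. *Participant Timeline* gives completion as the common rule, and no-shows are not enrolled in either arm. The difference in *Recruitment of Clinics and Patients* is at most loose wording.
- **Early arrival.** In intervention clinics "participating patients are asked to arrive up to 1 hour early for their scheduled visit". This is a request. Nothing in the article drops a patient who does not comply, and completing the battery is not an enrolment condition either. Intention-to-treat and per-protocol can therefore still differ among agreers.
- **Reading 12 v 10.8, 8.4 or 6.0 points as bias.** Under the assumptions of step 4 that gap is mainly dilution: a different target population, not a distorted estimate. The bias is what steps 2 and 3 describe.
- **Target population.** *Eligibility and Screening* aims at patients who would receive the intervention in usual care, which lends some support to an acceptor population. It does not resolve the problem, because controls are not restricted to would-be acceptors.
- **A positive result as an artefact.** The bound in step 3 is far below 8, so the documents do not support this.
- **Material not shown.** The study-flow figure and the statistical analysis plan may hold counts of decliners, so their absence from the article is no defect. However, an analysis plan can only analyse patients whose data are collected, and the article ties collection to enrolment.

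None of this removes the agreement condition, which is explicit, applies to one arm and is not repaired in any text shown. The limitations section does not mention it.

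**Conclusion.** The point holds for the agreement condition alone. As written, the primary comparison sets acceptors in intervention clinics against all SCQ-positive attenders in control clinics, and intention-to-treat is the wrong name for it.

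The size and direction of the bias cannot be found from the article, which gives neither a refusal rate nor outcomes of decliners. In the scenarios tabulated for no treatment effect, the spurious odds ratio runs from 0.66 to 1.52. Its ceiling is 1.44 at 70% uptake and 2.04 at 50%. These figures rest on a 2% underlying rate and on assumed uptake and relative rates. Selection alone could not plausibly produce the planned odds ratio of about 8. What is in doubt is how far the estimate, and the cost per case derived from it, measure the effect of the paradigm.

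**What to change.** 1. Define the intention-to-treat set identically in both arms: all SCQ-positive patients who complete the index visit, whether or not they agree to the 5-Cog. Make agreers or completers the per-protocol set.
2. Apply this from the start in clinics not yet open. As of December 2024, 12 of the 22 had completed onboarding.
3. In clinics already open, recover decliners by EMR extract. SCQ answers are documented in the EMR and outcomes are EMR based. The article says "we received a waiver of informed consent from individual patients from the IRB", but *EMR Data* links the waiver to enrolled patients. The IRB must confirm that it covers people who declined the testing; this should not be assumed.
4. Where decliner data cannot be obtained, describe the enrolled-only result as acceptors versus all control attenders, not as intention-to-treat.

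**Cost.** The work is a change of definition, an EMR extract and an IRB submission. The estimated effect will be smaller. If decliners have the 2% control rate, overall power is about 99%, 95% or 80% at 90%, 70% or 50% uptake. The heavier cost falls on the racial and ethnic minority subgroup, one of the two on which the sample size was based: power drops from 81% to about 75%, 60% or 42%. The amendment should state this openly.
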